##### 7.3.2. Predictors and moderators of response to treatment

Simple linear regression models will be used to observe any relationships between cognition/emotion composite scores at baseline and questionnaire scores after ATMX treatment to see if the objectively-measured cognition/emotion measures are related to the subjectively-measured ADHD symptom measures (ADHD-RS IV, CPRS-R). To examine the *predictive *relationship of cognition/emotion measures on ADHD symptom measures, changes after ATMX treatment in ADHD symptom measures will be categorized depending on whether or not they responded to the treatment. Analyses will be performed using two different definitions of treatment response: 1) ≥25% improvement and 2) ≥40% improvement; while non-response will be defined as 3) <25% improvement and 4) <40% improvement [11,17,19,52]. More specifically regarding the primary outcome, six predictors (the composite scores from baseline for the six cognition and emotional function markers, Table 1) will be used in logistic regression models to examine if baseline performance in these measures predict response to ATMX. Response in terms of the primary outcome will be defined initially as a ≥25% improvement (versus <25% improvement) in ADHD-RS IV and CPRS-R t scores (see Section 5). A secondary, more stringent definition of response will subsequently be implemented, using a response cut-point of ≥40%. With a planned sample size of >60, these analyses will be sufficiently powered. Further exploratory analyses may be performed at a later date.

Absolute change scores (continuous ADHD symptom data) will be used to see if the cognition/emotion measures *moderate *response to ATMX in ADHD symptom measures. These investigations will initially be performed on the total ADHD cohort, before examining any differences between those with and without comorbid anxiety.

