**Methods:**

Children and adolescents aged 6 - 17 y with ADHD will be enrolled. Clinical interview and validated scales will be used to confirm diagnosis and screen for exclusion criteria, which include concurrent stimulant use, and comorbid psychiatric or neurological conditions other than anxiety. Three assessment sessions will be conducted over the 13-week study period: Session 1 (Baseline, pre-treatment), Session 2 (six weeks, atomoxetine or placebo), and Session 3 (13 weeks, cross-over after one-week washout period). The standardized touch-screen battery, "IntegNeuro™", will be used to assess cognitive and emotional function. The primary measure of response will be symptom ratings, while quality of life will be a secondary outcome. Logistic regression will be used to determine predictors of treatment response, while repeated measures of analysis will determine any differences in effect of atomoxetine and placebo.

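### The stated test of whether baseline markers predict response to atomoxetine (ATMX) cuts symptom change at 25% and 40%, so that test (not the whole plan) loses about two fifths of the outcome information

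*Protocol article*

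**What the plan says.** Section 7.3.2 describes three analyses linking the baseline composites to symptoms.

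- **Relationship.** Simple linear regressions relate the baseline composites to questionnaire scores after ATMX (ADHD-RS IV, CPRS-R).
- **Prediction.** Change after ATMX is turned into response or non-response: "Analyses will be performed using two different definitions of treatment response: 1) ≥25% improvement and 2) ≥40% improvement". For the primary outcome, the six composites "will be used in logistic regression models to examine if baseline performance in these measures predict response to ATMX". The 25% cut on ADHD-RS IV and CPRS-R T-scores comes first; the 40% cut follows as a secondary, stricter definition.
- **Moderation.** "Absolute change scores (continuous ADHD symptom data) will be used to see if the cognition/emotion measures" moderate response.

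The Methods paragraph of the abstract names only the second of these for this question: "Logistic regression will be used to determine predictors of treatment response". On power, Section 7.3.2 says: "With a planned sample size of >60, these analyses will be sufficiently powered". It gives no effect size, response rate or power value.

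**The concern.** ADHD-RS IV and CPRS-R are completed by parents at all three sessions (Section 4.2.1), so a graded outcome is already in hand. After the cut, a child who improves by 24% counts the same as one who worsens, and a child who improves by 26% counts the same as one in full remission.

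The Results and Discussion section puts the question as whether baseline function can predict changes in symptom ratings, which is a graded quantity. The test labelled as predictive works on a coarser one. A marker that truly relates to outcome is then more likely to be missed, and whether it is found may depend on which cut is used. The article does not say what is concluded if the two cuts disagree.

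**Working it through.** **The plan's own figure.** The claim that more than 60 participants give sufficient power cannot be reproduced, because no inputs are stated. The n = 152 in Section 7.1 cannot stand in for it: that calculation concerns change in the inhibition and emotion measures, not prediction of response.

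**Inputs.**
- From the article: six predictors and the figure of more than 60 (Section 7.3.2); significance level 0.05 (Section 7.3); two-tailed testing and n = 152 (Section 7.1).
- Response rate: the only figure is up to 63.5% (Background). It is not tied to either cut-point, so a range is used.
- Assumed: normal outcome, linear marker effect, independent markers, and the correlation r between one true marker and the outcome.

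**Step 1: information kept by the cut.** For response rate p, the efficiency relative to the uncut outcome is φ(z_p)² / [p(1−p)].

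| p | kept | lost |
|---|---|---|
| 0.50 | 0.637 | 36% |
| 0.40 or 0.60 | 0.622 | 38% |
| 0.635 | 0.610 | 39% |
| 0.30 or 0.70 | 0.576 | 42% |
| 0.20 or 0.80 | 0.490 | 51% |

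**Step 2: effect on power.** Power after the cut = Φ[(1.960 + z_power) × √efficiency − 1.960]. If the continuous analysis has 80% power and p = 0.635: (1.960 + 0.842) × √0.610 − 1.960 = 0.228, and Φ(0.228) = 0.59, a drop of 21 points. At the same benchmark the drop is 19 points at p = 0.50, 23 at 0.30 or 0.70, and 30 at 0.20 or 0.80.

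**Step 3: simulation.** 1,500 runs per cell, six independent normal markers with one true effect, all six in both models, 63.5% responders. Power, linear versus logistic:

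| r | N = 152 | N = 61 |
|---|---|---|
| 0.20 | 68% vs 47% | 33% vs 22% |
| 0.25 | 87% vs 68% | 45% vs 31% |
| 0.30 | 96% vs 80% | 61% vs 42% |

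The gaps are 16 to 21 points at N = 152 and 11 to 19 at N = 61. A repeat with a fresh seed gave gaps of 12 to 22 and 9 to 21. With 40% responders at N = 152 the gaps were 20, 19 and 13.

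**Step 4: is it the right comparison?** The runs above cut the same normal variable that the linear model analyses, whereas the plan cuts percentage improvement. A separate simulation that cut percentage improvement and compared it with a baseline-adjusted linear model gave a loss of about 10 to 21 points, so the size holds.

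**Step 5: the smaller class.** With 61 participants and 63.5% responders there are 61 × 0.365 ≈ 22 non-responders for six predictors, or 22 / 6 ≈ 3.7 per predictor.

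**The case against.** The strongest reply is that two of the three analyses in Section 7.3.2 already keep the outcome continuous, and that the article nowhere says the logistic models override them. This largely stands. A reader might infer that the plan throws the continuous information away; it does not. What remains is narrower. The label of prediction, the link to the primary outcome and the abstract sentence all attach to the logistic models, while the continuous analyses carry other labels.

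Second, who reaches a response threshold is a fair clinical question for a trial meant to help clinicians choose treatment for an individual child. Both cuts are fixed in advance, ordered and referenced. That stands too, and is why the responder models should be kept. The cited sources are not at hand, so the documents do not support saying that the cut-points lack justification.

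Third, the article does not state baseline adjustment for the continuous analyses. A condensed article may leave that to the full plan, so it is no fault in itself.

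Fourth, prediction is not among the three numbered primary aims in the Background, and Section 5 introduces it as something to be determined as well. A reader might infer that the efficacy comparison or the sample size is weakened. Neither is: Section 7.3.3 analyses continuous variables by repeated-measures ANOVA, and n = 152 rests on change in the markers.

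**Conclusion.** The point holds for the stated predictive test only. With a roughly normal outcome and 30% to 70% responders, the cut costs that test about 36% to 42% of the information. For a single marker with r between 0.20 and 0.30, the cost is very roughly 10 to 20 points of power.

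The information figure is fairly stable over that range of response rates. The power figure is less so: it depends on an assumed correlation, and it grows if few or nearly all children respond (51% of the information at a 20% or 80% response rate). It would be wrong to read a precise power loss for this trial out of these numbers, since the article gives neither a correlation nor a response rate at its cut-points. The change is worthwhile because it is cheap and uses data already collected, not because a primary aim is at risk.

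**What to change.** In Section 7.3.2, make the lead prediction analysis a linear model of the continuous post-ATMX score, with the baseline value of the same score as covariate and the six baseline markers entered together. Fit it for ADHD-RS IV total and likewise for the CPRS-R T-scores named in the response definition, so that no planned outcome is dropped. State that the conclusion on whether the markers predict response rests on this model. Keep the ≥25% and ≥40% logistic models as supportive, clinically readable analyses, and amend the abstract sentence to match.

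The cost is wording: no new data, visits or participants. The downside is that the lead result becomes a slope in scale points rather than an odds ratio; the retained responder models still supply the latter.

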## Results and Discussion

The ACTION study will be a multi-site, double-blinded, randomized cross-over study examining the effects of ATMX on cognitive and emotional functions in children and adolescents with ADHD, whilst also identifying objective predictors of ATMX response in this group, including those with and without comorbid anxiety. The cross-over design of the study enables participants to act as their own controls when testing whether cognitive and emotional function at baseline is able to predict changes in symptom ratings after medication treatment. Enrolment and testing commenced in March 2008. Potential limitations in the study design pertain to the one-week washout period between treatment phases, and the absence of an "anxiety only" arm for examining comorbid anxiety outcomes. Although our selection of a washout period of one-week's duration was based on previous research [53-55], it is not known if any carry over effects were present. However, it is highly unlikely that the results obtained after six weeks of placebo treatment could be attributed to ATMX in those participants receiving active treatment (ATMX) in Phase A. Future studies may consider observing changes at first response and full response, and to vary the length of their washout periods between treatments. Additionally, an anxiety only arm should also be incorporated if investigating changes in comorbid anxiety outcomes.

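### Section 7.3.2 looks for predictors and moderators of atomoxetine response in ATMX-session outcomes alone, so it cannot separate markers of drug benefit from markers of general improvement

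*Protocol article*

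**What the plan says.** Section 7.3.2 sets out three analyses of the baseline markers.

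- **Association.** Simple linear regressions examine "relationships between cognition/emotion composite scores at baseline and questionnaire scores after ATMX treatment".
- **Prediction.** The article states that "changes after ATMX treatment in ADHD symptom measures will be categorized depending on whether or not they responded to the treatment". The definition is: "Response in terms of the primary outcome will be defined initially as a ≥25% improvement (versus <25% improvement) in ADHD-RS IV and CPRS-R t scores". A stricter version follows, "using a response cut-point of ≥40" per cent. The six marker composites "will be used in logistic regression models to examine if baseline performance in these measures predict response to ATMX".
- **Moderation.** "Absolute change scores (continuous ADHD symptom data) will be used to see if the cognition/emotion measures" act as moderators of the response to ATMX.

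Placebo is not mentioned in 7.3.2. It enters the analysis in 7.3.3, a repeated measures ANOVA of baseline, ATMX and placebo, in the total cohort and then by comorbid anxiety. The covariates listed there concern previous stimulant treatment and its interaction with anxiety; the six markers are not among them.

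Under Section 1, every child receives both compounds and is assessed after each. The Results and Discussion section appeals to this when it describes testing whether baseline function predicts symptom change: "The cross-over design of the study enables participants to act as their own controls".

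**The concern.** A child may improve on atomoxetine because of the drug, or because of expectation, regression to the mean or the passage of time. A marker related to any of the latter will be associated with improvement in the ATMX phase even if the drug benefits every child equally. The child's placebo phase is the comparison that separates these explanations, and 7.3.2 does not use it. The word moderation makes the gap plain: a moderator changes the difference between two treatments, and one condition contains no difference.

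The Background says the results should help clinicians decide when to consider non-stimulants for an individual child, and the Abstract speaks of personalized medicine. A marker of general improvement, presented as a predictor of ATMX response, would misinform that decision.

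**Working it through.** **The plan's own figures.** Section 7.1 gives 152 participants (power 0.9, two-sided alpha 0.05) without the mean difference or SD, so the number can only be inverted. With 1.960 + 1.282 = 3.242, it corresponds to d = 3.242 × √(2/152) = 0.372 for two groups of 152, or to a standardized within-child difference of 3.242/√152 = 0.263 if read as paired. Nothing below depends on this. For the predictor models, 7.3.2 cites only a planned sample above 60, so results are shown for N = 152 and for N = 60 or 61.

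**Algebra.** Let M be the baseline marker and write improvement in child i as

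- ATMX: A = a + δ + (β + γ)M + u + e₁
- placebo: P = a + βM + u + e₂

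Here β is the general prognostic effect, δ the drug effect at M = 0 and γ the change in drug effect per unit of M. Regressing A on M estimates β + γ; regressing A − P on M estimates γ. ATMX data alone cannot separate the two at any sample size. The confusion runs both ways: β and γ of opposite sign can hide a true predictor.

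**Simulation, γ = 0 throughout.** The prognostic strength is assumed, so a range is shown.

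*Set-up 1.* One marker; improvement = 1.0 + b·M + noise under ATMX and 0.4 + b·M + noise under placebo; noise SD 0.9, correlation 0.5 between phases; response = improvement ≥ 1.0. At b = 0.3 the marker–improvement correlation is 0.3/√(0.09 + 0.81) = 0.316. Ranges cover repeated runs, with and without a period effect.

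| b | ATMX-only logistic, N = 152 | ATMX-only logistic, N = 61 |
|---|---|---|
| 0 | about 5% | about 5% |
| 0.1 | 15–19% | about 10% |
| 0.2 | 54–58% | about 25% |
| 0.3 | 87–89% | 47–50% |

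Regression of A − P on the marker rejects in about 5% at both sizes, as it must, because M cancels from the difference. When the same logistic model is fitted to the placebo phase at N = 152, it flags the marker in 16%, 50% and 83% of trials at b = 0.1, 0.2 and 0.3. The planned model thus finds predictors almost as readily where there is no drug.

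*Set-up 2.* Six independent markers, the first with correlation r to improvement in both phases; within-child correlation 0.4; response 63.5% under ATMX (the upper value in the Background) and 30% under placebo (assumed); 2,000 runs per row.

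| r | Logistic, N = 152 | Absolute change, N = 152 | A − P, N = 152 | Logistic, N = 60 | A − P, N = 60 |
|---|---|---|---|---|---|
| 0 | 5.0% | 4.5% | 5.4% | 5.0% | 5.3% |
| 0.1 | 16.8% | 23.4% | 4.8% | 9.7% | 5.4% |
| 0.2 | 47.2% | 68.8% | 5.0% | 23.6% | 5.0% |
| 0.3 | 82.6% | 95.6% | 4.7% | 42.6% | 4.4% |
| 0.4 | 97.9% | 99.9% | 4.8% | 64.9% | 4.7% |

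With within-child correlation 0.2 or 0.6 (r = 0.3, N = 152), the logistic figure is 83.4% or 84.0% and the A − P figure 6.0% or 4.8%. The absolute-change column shows that the continuous moderator analysis shares the problem.

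**The case against.** The strongest reply is that the harm is conditional. Nothing in the article shows that any of the six markers is prognostic for improvement regardless of treatment, and with no such link the planned model keeps its 5% error rate. That stands. A reader might infer that prognostic markers will be reported as drug predictors; the documents support only that they can be, and that the analysis could not reveal it.

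It may also be said that an article condenses a fuller plan. Here, though, 7.3.2 fixes the outcome, cut-points, predictors and model, and its outcomes do not match the own-control rationale in the Discussion.

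Other stronger readings do not hold:

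- The simple linear regressions might be called invalid because they omit baseline symptom scores. Their stated purpose is association: they use "questionnaire scores after ATMX treatment to see if the objectively-measured cognition/emotion measures are related to the subjectively-measured ADHD symptom measures". Prediction is introduced separately.
- The plan might be said to discard continuous information. It dichotomizes for the logistic models but also plans a continuous change analysis.
- Improvement might be taken as explicitly measured from baseline. That is a reasonable inference, since 7.3.3 uses baseline-to-ATMX comparisons, but 7.3.2 does not state the reference.
- The main efficacy result might be thought biased. Efficacy and the anxiety comparison rest on 7.3.3, which does compare ATMX with placebo.

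Finally, the Background speaks of choosing non-stimulants over stimulants or non-pharmacologic care. A placebo contrast does not settle that choice either. This limits what the trial can claim, but it does not rescue an analysis with no comparator.

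**Conclusion.** The point holds as a defect of the predictor and moderator analyses and should be fixed before they are run. That they cannot separate β from γ is algebraic and needs no assumption. The error rates do need assumptions: a marker equally prognostic in both phases, a constant drug effect, no carry-over, and response defined by a cut on a standardized change rather than by 25% or 40% of an actual score. Under these, the chance of labelling a purely prognostic marker a predictor of ATMX response runs from the nominal 5% with no prognostic link to nearly 90% at a slope of 0.3 with N = 152, and to about 50% with N = 61. No single figure in that range should be quoted alone. Baseline-marker prediction is an added objective beside the three primary aims, and the 7.3.3 comparisons are untouched, so this is a should-fix point and not a threat to the trial's main result.

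**What to change.** Make the main predictor and moderator analysis a model of the continuous ADHD-RS IV total from Sessions 2 and 3, with baseline ADHD-RS IV, period, treatment, marker and marker × treatment, and a random effect for child. Interpret only the marker × treatment coefficient as predicting or moderating drug response. Regressing the within-child ATMX-minus-placebo difference on the marker, adjusted for sequence, is an acceptable alternative. With complete data and equal variances the two give the same coefficient, because the baseline score and the marker's main effect are constant within a child and cancel.

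Keep the 25% and 40% responder models as descriptive, shown side by side for the ATMX and placebo phases; state that improvement is measured from baseline, if that is meant; and call ATMX-only associations prognostic.

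The cost is analysis wording only, since both phases are already recorded for every child. Fewer markers will reach significance, because general prognosis no longer counts towards the result. Power for the interaction will also be lower where the residual correlation ρ between phases is below 0.5, since the difference then has variance 2σ²(1 − ρ) > σ². The contrast still assumes no carry-over across the one-week washout, which the Discussion already lists as a limitation.

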### 4. Data collection

#### 4.1. Screening measures

Attention Deficit Hyperactivity Disorder Rating Scale-IV (ADHD-RS IV) [39] The ADHD-RS IV will confirm DSM-IV diagnosis and subtype of ADHD, indicated by a score >1 in six or more items in the Inattentive and/or Hyperactive-Impulsive sections of the scale. If a DSM-IV diagnosis cannot be confirmed using the ADHD-RS IV, the participant will be excluded. Total scores will be used as a measure of symptom severity.

Clinicians will also undertake the Anxiety Disorders Interview Schedule for DSM-IV: Child Version (ADISC: Parent Interview Schedule) [36]. Scores of ≥4 for any of the domains are indicative of a positive diagnosis. Participants will be categorized as having either ADHD + comorbid anxiety (i.e., Separation anxiety disorder, Obsessive compulsive disorder, and/or Generalized anxiety disorder [36]); or ADHD without anxiety (which includes those with other comorbidities excluding anxiety). The number of diagnosed comorbidities in total, including anxiety and others, will also be recorded.

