#### 4.2. Baseline (Session 1), Session 2 and Session 3 measures

##### 4.2.1. ADHD symptom severity

At each testing session parents will complete the ADHD-RS IV, as a measure of ADHD symptom severity.

Parents will also rate symptom severity on the Conners' Parent Rating Scale - Revised (Long version; CPRS-R) [40]. The CPRS-R ratings will provide a second assessment of symptom severity, providing a within-study check on the consistency of symptom ratings. T-scores for all 13 subscales will be recorded, where larger T-scores indicate greater impairment.

The secondary outcomes of ACTION will be the relationships between the primary cognitive measures and ratings obtained from the ADHD-RS IV and CPRS-R.

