### 7. Statistical analysis

#### 7.1. Sample size

The data used for the power calculation of the inhibition function primary outcome measures are from a sample of 175 ADHD individuals assessed off and then on stimulant medication (methylphenidate or dexamphetamine; data not published). The power calculation of the emotional function primary outcome measures are based on a sample of 30 ADHD participants from the same sample.

Power was set at 0.9, alpha level at 0.05, and the mean difference (change in off-versus on-medication) and standard deviations for the mean of the n = 175 group was used. The means for the n = 30 group were set at '0', since there was no change expected in these outcome measures for the placebo group. After applying the pilot data means from each primary outcome measure the highest sample size estimate we obtained was n = 152 for each group under two-tailed conditions. Therefore, a minimum total of 152 participants are required in this cross-over study to achieve the desired level of probability in detecting a statistically significant difference across the two primary outcome measures.

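### Percentage cut-points on CPRS-R T-scores have no fixed meaning: the CPRS-R response rule in Section 7.3.2 depends on baseline and is very severe at 40%

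*Protocol article*

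**What the plan says.** Section 7.3.2 sets the outcome for the logistic response models. Response is initially "a ≥25% improvement (versus <25% improvement) in ADHD-RS IV and CPRS-R t scores". The section then adds: "A secondary, more stringent definition of response will subsequently be implemented, using a response cut-point of ≥40" per cent. The explanatory side is fixed too: "six predictors (the composite scores from baseline for the six cognition and emotional function markers, Table 1) will be used in logistic regression models". On size it says: "With a planned sample size of >60, these analyses will be sufficiently powered".

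Section 4.2.1 confirms the CPRS-R metric: "T-scores for all 13 subscales will be recorded, where larger T-scores indicate greater impairment". Section 4.1 describes the ADHD-RS IV differently: "Total scores will be used as a measure of symptom severity". The T-score label in Section 7.3.2 is therefore most naturally read as belonging to the CPRS-R alone.

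The article does not say whether the two scales are judged separately or must both be met. It also does not say which of the CPRS-R subscales listed in Section 5 decides response.

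**The concern.** A percentage change needs a scale whose zero means something. T=0 is only the point five SDs below the population mean. The rule therefore does not ask for a quarter or two-fifths of a child's symptoms to go. It asks for a number of T points that varies with baseline and that answers to a different share of the child's excess over the norm at each baseline.

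Two things are at stake. The CPRS-R responder classes would not mean the same from child to child, or the same as the ADHD-RS IV classes at the same nominal cut-point, so the two scales could disagree because of the metric alone. And a severe rule leaves few responders for a six-predictor logistic model. Because the bar moves with baseline severity, a baseline marker that tracks severity could also appear to predict response partly through the rule.

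**Working it through.** **The plan's own figure.** The article calls a sample above 60 sufficient for the response models but gives no response rate, odds ratio or power, so the figure cannot be reproduced. It equals 6 predictors × 10 participants, but the article does not say that this is its origin. A logistic model is limited by the smaller outcome class, not by participants.

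**Inputs from the article.** Cut-points 25% and 40%; six predictors; N just above 60 (61 used); and N=152 from Section 7.1 ("a minimum total of 152 participants are required in this cross-over study").

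**Assumed inputs.** T metric with mean 50 and SD 10. Baseline mean 65 to 80 (SD 8, values held within 50 to 90), mean fall 5 to 15 points, SD of change 8 to 12, lowest attainable T-score 38. The article gives none of these.

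**Step 1: what the rule requires.** For baseline B, the required fall is 0.25B or 0.40B, and the share of the excess over the norm is fall/(B − 50).

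| B | 25%: fall, end point | share of excess | 40%: fall, end point | share of excess |
|---|---|---|---|---|
| 60 | 15, to 45 | 15/10 = 150% | 24, to 36 | 24/10 = 240% |
| 70 | 17.5, to 52.5 | 17.5/20 = 88% | 28, to 42 | 28/20 = 140% |
| 80 | 20, to 60 | 20/30 = 67% | 32, to 48 | 32/30 = 107% |

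**Step 2: the result depends on the choice of standard score.** T=70 is z=2. A 25% fall in z is 0.5 SD, or 5 T points, to T=65. A 25% fall in T is 17.5 points. Same child, same percentage, two different rules.

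**Step 3: a single-baseline check.** With every child at T=70, a mean fall of 8 and SD 9, P(fall ≥ 17.5) = P(Z ≥ 9.5/9) = 14.6%, or 22 of 152. P(fall ≥ 28) = P(Z ≥ 20/9) = 1.3%, or 2 of 152.

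**Step 4: simulation over the assumed ranges.** Sixty scenarios were run: four baseline means, five mean falls and three SDs, with 400,000 draws each. Responders per predictor = N × P(response)/6; responders are the smaller class throughout.

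| | 25% | 40% |
|---|---|---|
| P(response), range | 3.5% to 43.5% | 0.1% to 9.9% |
| Middle case (baseline 70, fall 10, SD 10) | 22.7% | 2.5% |
| Responders per predictor, N=61 | 0.4 to 4.4 | about 0 to 1.0 |
| Responders per predictor, N=152 | 0.9 to 11.0 | 0.02 to 2.5 |

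At N=152 and 25%, five of the 60 scenarios reach ten responders per predictor (a conventional yardstick, not the article's). All five have a mean fall of 15 and a baseline mean of 65 or 70. With the drug effect held at a mean fall of 10 (SD 10), the 25% response rate drifts from 25.5% at a baseline mean of 65 to 16.5% at 80.

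**Step 5: sensitivity to the floor.** With a floor of 38, no child below 38/0.60 = 63.3 can meet 40%. Repeating the simulation without a floor raises the top 40% case to about 18.7%: 152 × 0.187/6 = 4.7 responders per predictor, still few. The 25% range hardly moves (3.5% to 45.9%).

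**The case against.** The strongest reply concerns scope. A reader might infer that almost no child can meet either cut-point and that the response models as a whole lack events. The article does not support that. At 25%, the initial definition, the assumed inputs give about 4% to 44%: demanding, but attainable. Near-unattainability applies to the 40% rule, which the article itself ranks second. Every response rate here also rests on baseline and change values that the article does not give, so the shortage of responders is a range under assumptions and not a documented fact.

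The ADHD-RS IV models are also untouched, since Section 4.1 describes that scale by total scores. The CPRS-R limit would reach them only if the joining word in the definition means that both scales must be met, which the text leaves open. It is tempting to set the simulated rates against the response of up to 63.5% in the Background, but that figure comes with no scale or cut-point and cannot serve as a benchmark.

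Other planned analyses limit the damage. Section 7.3.2 also has linear regression on post-treatment questionnaire scores and a moderator analysis on absolute change, and Section 7.3.3 analyses continuous variables. None uses the cut-points. Section 4.2.1 gives the CPRS-R a supporting role, and response prediction is not among the three primary aims in the Background.

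All of this stands. It narrows the point and lowers its weight, but none of it gives a percentage of a T-score a meaning.

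**Conclusion.** The point holds for the CPRS-R half of the response definition. That 25% and 40% of a T-score have no fixed meaning follows from the metric and needs no assumption about the data. The required share of excess at 25% runs from 150% at T=60 to 67% at T=80, and from T=70 the 40% rule ends at 42, below the population mean.

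The size of the responder shortage does rest on assumptions. Within the stated ranges, the 40% six-predictor CPRS-R model has at most about 2.5 responders per predictor at N=152 (about 4.7 with no floor), and the 25% model is thin in most scenarios but not all. A reader might go further and conclude that the efficacy comparison is compromised. It is not: the randomised atomoxetine–placebo comparison and the sample size in Section 7.1 do not use the cut-points. This should be fixed, but it is not a fault that undermines the trial.

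**What to change.** Change the definition in Section 7.3.2, before unblinding, as follows.

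- Keep the 25% and 40% cut-points for the ADHD-RS IV total score.
- For the CPRS-R, define response by a fixed T-point or reliable-change threshold, or by percent change in raw subscale scores.
- State that the two scales are judged separately.

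Making the ADHD-RS IV the only primary response definition would be a further choice and is not needed for this repair.

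The cost is about one sentence. No new data are needed: raw scores underlie the T-scores, and Section 7.2 has the paper questionnaires entered into scoring spreadsheets. The drawback is that CPRS-R response rates become less directly comparable with any studies that used percentage cut-points.
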